#### Secondary Outcomes

##### Physical Activity

Objectively measured purposeful MVPA adherence (ie, MVPA10+) will be assessed by triaxial accelerometry (Actigraph GT3X-BT, Actigraph, Pensacola, Florida, USA) at baseline and 3-, 6-, 9-, and 12-month follow-up. MVPA10+ is appropriate for measuring purposeful exercise [51] and provides a conservative estimate of exercise adherence. Participants will be instructed to wear the accelerometer on their right hip for 7 consecutive days at each measurement time point. Participants will be instructed to remove the accelerometer during sleep and for water-based activities. Accelerometers will be initialized and downloaded using ActiLife version 6.11. Epoch lengths will be specified at 5 seconds and will be summed as counts per minute. Nonwear time will be classified as 90 minutes of consecutive zeros, allowing for nonzero counts up to 2 minutes; if no counts are detected during the 30-minute counts before and after this interval [52], these data will be classified as nonwear time and excluded from analysis. Participants must have a total of ≥10 hours of valid wear time per day to be included in the analyses [53]. Our pilot work confirmed that recovery intervals during HIIT register as moderate-to-vigorous activity, not interruptions to physical activity. Freedson cut points [54] will be used to identify time spent in moderate (1952-5724 counts/min), vigorous (≥5725 counts/min), and MVPA (≥1952 counts/min) during wear time on valid wear days. Time spent in the various intensities will be averaged across valid wear days and multiplied by 7 to provide a weekly estimate of physical activity at each measurement time point. Purposeful exercise will be operationalized as minutes spent in MVPA10+ [54], in line with physical activity guidelines, which specify that bouts of physical activity should be accumulated in bouts of 10 minutes or more. Furthermore, given that participants in HIIT are prescribed 75 minutes of purposeful exercise per week (ie, 3×25-min HIIT sessions) and participants in MICT are prescribed 150 minutes per week (ie, 3×50-min MICT sessions) and that physical activity guidelines highlight the equivalency of 75 minutes of vigorous exercise and 150 minutes of moderate exercise, additional supplemental analyses will be conducted, whereby each vigorous minute of exercise within the identified MVPA10+ bouts will be credited as 2 minutes. This approach was carefully considered for the adherence measure and justified in the grant application for this trial. As such, this modified MVPA10+ outcome represents an appropriate measure of purposeful exercise [51] and allows for a direct assessment of adherence to HIIT or MICT.

Self-reported physical activity adherence will be assessed through an exercise log completed through the mobile application. Participants will be asked to record (1) whether exercise was complete, (2) type of exercise completed, (3) the duration of the exercise, (4) the number of intervals conducted (for the HIIT condition exclusively), and (5) how hard the session was (Rating of Perceived Exertion scale; [55]). The percentage adherence will be calculated (ie, number of exercise sessions divided by the number of prescribed sessions multiplied by 100% [56]).

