### High-Intensity Interval Training Protocol

HIIT involves sessions of 4 to 10 ×1-minute high-intensity intervals (cycling *sprints*, uphill treadmill walking, uphill outdoor walking, and elliptical machine) at approximately 80% to 90% peak oxygen uptake (VO_2_ peak), interspersed with 1-minute rest periods at approximately 40% VO_2_ peak. Results from the pilot study preceding this randomized controlled trial demonstrated that individuals with prediabetes respond well to this protocol [30].

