### Transition to Independent Exercise

The 2-week supervised exercise training program will incorporate 3 unsupervised sessions to enable participants to practice engaging in exercise independently. Following completion of the 2-week program, participants will be asked to engage in their randomized exercise protocol (ie, HIIT or MICT) a minimum of 3 times per week for the next 12 months. Specifically, participants in HIIT will be prescribed a 5-minute warm-up, 10 ×1-minute high-intensity intervals, and a 5-minute cooldown. Participants in MICT will be prescribed 50 minutes of moderate-intensity exercise.

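### Between arms, MVPA10+ minutes measure activity volume, not adherence: the prescriptions differ by 75 min/week, and the 2-for-1 vigorous credit closes that gap only if the whole 25-minute HIIT session is vigorous

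*Protocol article*

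**What the plan says.** The Physical Activity section under Secondary Outcomes presents MVPA10+ as the objective measure of adherence. It gives the weekly prescriptions: "participants in HIIT are prescribed 75 minutes of purposeful exercise per week (ie, 3×25-min HIIT sessions", and 150 minutes for MICT as three 50-minute sessions. Because guidelines treat 75 vigorous and 150 moderate minutes as equivalent, it adds supplemental analyses in which "each vigorous minute of exercise within the identified MVPA10+ bouts will be credited as 2 minutes". It concludes that the modified outcome "allows for a direct assessment of adherence to HIIT or MICT".

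The session content is described elsewhere:

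- Transition to Independent Exercise: both arms exercise "a minimum of 3 times per week for the next 12 months". For HIIT, "participants in HIIT will be prescribed a 5-minute warm-up, 10 ×1-minute high-intensity intervals, and a 5-minute cooldown". For MICT, "Participants in MICT will be prescribed 50 minutes of moderate-intensity exercise".
- High-Intensity Interval Training Protocol: the one-minute efforts at about 80% to 90% of VO2 peak are "interspersed with 1-minute rest periods at approximately 40% VO_2_ peak".
- Table 1 under Supervised Exercise Training repeats that interval definition and puts MICT at about 45% to 55% of VO2 peak.

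Proposed Data Analyses handles accelerometer outcomes in the same way as fitness, that is, as a HIIT v MICT comparison in a mixed model adjusted for baseline, and mentions no scaling to the prescribed minutes. The Physical Activity section also defines a self-reported adherence percentage: "number of exercise sessions divided by the number of prescribed sessions multiplied by 100".

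**The concern.** A between-arm measure of adherence should give the same value when both arms follow their prescriptions equally well. Minutes cannot do that when one arm is asked for half as many as the other. The credit is meant to repair this, but the equivalence behind it is between 75 vigorous and 150 moderate minutes, and the HIIT prescription is not 75 vigorous minutes.

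Study Design describes the trial as a comparison of adherence to the two modalities. If unscaled or credited minutes are read as adherence, equal and complete adherence would appear as lower adherence in HIIT. Adjusting for baseline activity does not help, because the two prescriptions begin after randomization.

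**Working it through.** **Inputs.** Three sessions per week in both arms (the stated minimum). MICT session 50 minutes. HIIT session 25 minutes as stated under Physical Activity, or built from its parts: 5 + 10 + 5 = 20 minutes without recoveries, 29 with nine one-minute recoveries, 30 with ten. Ten high-intensity minutes per session.

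**The plan's own figures.** MICT: 3 × 50 = 150. HIIT: 3 × 25 = 75. Both products are right. The 25-minute session, however, is not the sum of the listed components, which give 20 or 29 to 30 minutes (60 or 87 to 90 a week).

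**Formulas**, with L the HIIT session length and v its vigorous minutes:

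- Raw HIIT minutes per week = 3L; raw gap = 150 − 3L.
- Credited HIIT minutes = 3(L + v); remaining gap = 150 − 3(L + v).
- The credited gap is zero when 3(L + v) = 150, so v = 50 − L.

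**Full adherence in both arms, v = 10:**

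| L (min) | HIIT raw/week | Raw gap | HIIT credited/week | Remaining gap | v needed for zero gap |
|---|---|---|---|---|---|
| 20 | 60 | 90 | 90 | 60 | 30 (impossible) |
| 25 (stated) | 75 | 75 | 105 | 45 | 25 of 25 |
| 29 | 87 | 63 | 117 | 33 | 21 of 29 |
| 30 | 90 | 60 | 120 | 30 | 20 of 30 |

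On the stated session, a fully adherent HIIT arm would show 75/150 = 50% of the MICT minutes uncredited and 105/150 = 70% credited.

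**Sensitivity to v.** Vigorous time is defined by an accelerometer cut point (5725 counts/min or more), and the article does not report how many HIIT minutes reach it.

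- v = 0: the credit adds nothing and the gap stays at 60 to 90.
- v = 20, the whole block of intervals and recoveries: the gap is 150 − 3 × 45 = 15 for a 25-minute session and 150 − 3 × 50 = 0 for a 30-minute session.

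The second case is hard to square with recoveries at about 40% of VO2 peak, below the 45% to 55% that the plan treats as moderate. The article reports that recoveries register as moderate-to-vigorous in the pilot. That keeps the bout unbroken; it does not show that they count as vigorous.

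**The case against.** The strongest reply is that nothing is hidden. The 75 v 150 difference is printed in the article, the credit was added because of it, and the credit applies only to vigorous minutes actually observed. It is also supplemental, the primary outcome is VO2 peak, and a second adherence measure exists that is relative to prescription and unaffected by session length. In the pilot, moreover, HIIT participants did more vigorous activity at one month and more moderate activity at six months, so the observed data need not favour MICT.

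Most of this stands and limits the point. It does not rescue the statement that the credited minutes assess adherence directly, because its rationale still requires a session that is vigorous throughout. The pilot results describe activity achieved; they do not make the two prescriptions equal in minutes.

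A reader might be tempted to go further in three ways, none of which the documents support:

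- **A probability of a false adherence finding.** This would need complete adherence by everyone, together with the SD of 16 min/day from Sample Size. That SD comes from a population survey of MVPA, not from MVPA10+ under full adherence. A simple calculation would also treat one time point, whereas the plan uses a baseline-adjusted repeated-measures model. Nor is the gap directly comparable with the 10 min/day target, which is described as a within-condition increase.
- **A faulty self-report percentage**, because no rule on type, length or a cap is printed. The article condenses a fuller protocol, such rules commonly sit there or in the analysis plan, and the app records type, duration and intervals. Silence here is not an error.
- **MVPA10+ as useless.** It remains sound as activity volume and for change within an arm.

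**Conclusion.** The point holds in limited form. As written, neither raw nor credited MVPA10+ supports a between-arm conclusion about adherence. With full adherence in both arms, the raw gap is 75 min/week on the stated prescription (60 to 90 across session lengths). After the credit it is 45 (30 to 60), provided that exactly ten minutes per HIIT session count as vigorous. Without any vigorous minutes it stays at 60 to 90; with the whole interval block vigorous it falls to 0 to 15.

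These figures also assume exactly three sessions a week, that the whole session counts towards MVPA10+, and that other bouted activity is absent or equal in the arms. In addition, the 25-minute HIIT session conflicts with the listed components. This check does not say which is right. The consequence is confined to how a secondary outcome and a supplemental analysis may be interpreted.

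**What to change.** 1. Report and interpret raw and credited MVPA10+ between arms as activity volume. Delete or correct the statement that the credited version assesses adherence directly.
2. Base the between-arm adherence conclusion on the self-reported percentage of prescribed sessions, which is neutral to session length.
3. Reconcile the HIIT session length between Physical Activity (25 minutes) and the content given in Table 1, High-Intensity Interval Training Protocol and Transition to Independent Exercise (20 or 29 to 30 minutes).
4. If MVPA10+ as a proportion of each arm's prescribed minutes is wanted, add it only as a sensitivity analysis, and state that non-prescribed activity inflates the arm with the smaller denominator. For example, 60 min/week of ordinary walking would score 60/105 = 57% in HIIT and 60/150 = 40% in MICT on credited denominators (60/75 = 80% v 40% on raw ones).

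No new data are needed. The changes are to labelling, wording and, if the sensitivity analysis is added, one derived variable. The downside is small: the accelerometer result supports a narrower statement.

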##### Psychological Measures

Task self-efficacy, self-regulatory efficacy, concurrent self-regulatory efficacy, outcome expectations, and self-monitoring will be assessed at baseline, post intervention, and at 6- and 12-month follow-up (see Table 2 for specific details on study measures). Additional psychological variables that will be assessed include (1) exercise enjoyment measured at baseline, post intervention, and at 6- and 12-month follow-up [57]; (2) instrumental and affective attitudes measured at baseline, post intervention, and at 12-month follow-up (adapted from Conner et al [58]); and (3) affective state measured at baseline, post intervention, and at 12-month follow-up [59].

On training days 1, 6, and 10, counselors will ask participants to rate their in-task affect [60] and rating of perceived exertion [55] at the beginning (2.5%), middle (42.5%), and end (92.5%) of workout completion in both conditions (percentages indicate the proportion of workout completion to ensure this was matched across sessions of different lengths). In addition, participants will be asked to rate their exercise enjoyment halfway through the exercise session (50% of workout completion) in both conditions.

##### Anthropometric and Demographic Measures

Body mass, height (SECA, 700 SECA Hamburg Germany), waist circumference (measured at the level of the umbilicus), and blood pressure (measured manually using a sphygmomanometer) will be measured in the morning after an overnight fast at baseline, post intervention, and at 6- and 12-month follow-up using standard procedures. Information on ethnicity, household income, marital status, education level, medication history, and current smoking status will be collected at baseline.

##### Body Composition

Dual-energy x-ray absorptiometry (Hologic Discovery A) scans will be used to assess percentage body fat mass at baseline, post intervention, and at 12-month follow-up.

##### Biochemical Variables

A qualified and experienced phlebotomist will obtain a blood sample in the fasted state (≥8 hours overnight fast) and exactly 30 minutes following consumption of the 75 g glucose drink (Trutol, Fisher Scientific) from an antecubital vein. Samples will be placed on ice and processed within 30 minutes to obtain plasma via centrifugation for 15 minutes at 1550 g at 4℃.

**Table 2 table2:** Description of psychological constructs assessed in the *Small Steps for Big Changes* program.

Outcome	Measure	Items	Exemplar question	Response options
Task self-efficacy	Study-specific. Created following recommendations made by Bandura [25] and McAuley and Mihalko [61]	4	How confident are you that you can perform 4-high intensity intervals OR perform 20-minutes of continuous moderate exercise (dependent on condition)	0% (not at all) to 100% (extremely confident)
Self-regulatory efficacy	Study-specific. Adapted from Shields and Brawley [62]	14	How confident are you that you can develop solutions to cope with time management challenges with respect to your exercise schedule?	0% (not at all) to 100% (extremely confident)
Concurrent self-regulatory efficacy	Study-specific. Adapted from Jung et al [19]	5	During a typical week, how confident are you in your ability to concurrently manage high-intensity interval training /continuous moderate intensity exercise amongst your other valued life goals? (dependent on condition)	0% (not at all) to 100% (extremely confident)
Outcome expectations: likelihood	Study-specific. Adapted from Locke et al [31]	23	How likely is it that each outcome in the list below will occur at least once in a typical week for the next four weeks as a result of engaging in high-intensity interval training/moderate intensity continuous training (dependent on condition) Lower risk of type 2 diabetes; Feel good about my physical appearance	1 (very unlikely) to 9 (very likely)
Outcome values	Study-specific. Adapted from Locke et al [31]	23	How much do you value attaining each outcome from the list below? Lower risk of type 2 diabetes; Feel good about my physical appearance	1 (little value to me) to 9 (great value to me)
Self-monitoring	Study-specific. Adapted from Hallam and Petosa [63] and Petosa [64]	19	In the past week I mentally kept track of my exercise activities	1 (never) to 5 (very often)
Affective and instrumental attitudes	Study-specific. Adapted from Connor et al [58]	13	For me, exercising three days per week would be...1 (useless) to 7 (useful)	1 to 7 (anchors vary depending on the question)
Affective state	The Positive and Negative Affect Schedule (PANAS; [59])	20	Read each item and then use the scale to indicate to what extent you have felt this way during the past few days (Interested, Distressed, Upset)	1 (very slightly or not at all) to 5 (extremely)
Enjoyment	Physical activity enjoyment scale (PACES; [57])	18	Please rate how you feel at the moment about the physical activity you have been doing...1 (I enjoy it) to 7 (I hate it)	1 to 7 (anchors vary depending on the question)
In-task affect	Feeling Scale [60]	1	When asked please tell me how you feel at that current moment using the scale below	+5 (very good) to −5 (very bad)
In-task rating of perceived exertion	10-point Category-Ratio Scale [55]	1	Using the scale provided please rate how hard you are currently working	0 (no exertion at all) to 10 (maximal exertion)
In-task exercise enjoyment	Study-specific	1	Using the scale provided please rate how much you are enjoying this exercise session	1 (note at all) to 7 (extremely)

Samples will be batch-analyzed in duplicate after storage at −80℃. Plasma glucose will be assessed via the enzymatic hexokinase method using a commercial assay (Pointe Scientific) on a clinical chemistry analyzer (Chemwell 2910, Awareness Technologies). Insulin will be measured by enzyme-linked immunosorbent assay (Mercodia, Upsula, Sweden), as described previously [65]. Glucose (mmoL/L) and insulin (mU/L) values will be used to calculate homeostasis model assessment of insulin resistance using the Web-based Homeostasis Model Assessment-2 calculator, a validated method that is highly correlated (*r*=.88) with the hyperinsulinemic-euglycemic clamp [66] and is sensitive to change following exercise interventions [65,67,68]. Oral glucose disposition index will be used to assess beta-cell function and will be calculated based on the hyperbolic relationship between glucose-stimulated insulin secretion (change in plasma insulin divided by the change in plasma glucose from fasting to 30 minutes) and insulin sensitivity (1/fasting insulin, as described by Utzschneider et al [68]). The inflammatory marker C-reactive protein will also be assessed. Postintervention samples will be obtained approximately 48 hours following the last supervised training session and at 12-month follow-up.

##### Continuous Glucose Monitor

CGM will take place using the iPro 2 Professional CGM and Enlite sensor (Medtronic MiniMed, Northridge, CA) in a subsample of participants. The first 20 participants randomized in the trial will be invited to participate in the CGM assessment. The CGM records glucose values in a blinded fashion using a small microneedle inserted into the subcutaneous abdominal adipose tissue that is connected to a recorder that quantifies interstitial glucose values every 5 minutes. Finger-stick blood glucose samples are taken 4 times per day and are analyzed by a software program (CareLink Pro) upon device removal and downloaded to create 24-hour blood glucose curves. CGM data will be analyzed for (1) average blood glucose, (2) 2-hour postprandial area under the glucose curve, (3) postmeal spikes, and (4) glycemic variability (mean amplitude of glycemic excursions and SD). Participants who wear a CGM will be provided a standardized diet (approximately 24 kcal/kg, approximately 60% carbohydrates, approximately 27% fat, and approximately 13% protein) to consume during the day before and on the day of each 24-hour monitoring period. CGM data will be collected for 24 hours at baseline and beginning approximately 24 hours after the last day of supervised training. To accurately interpret CGM data, each participant will consume the same meals at the same times of the day during each assessment period.

### Participant Safety

The primary safety concerns for participants in this trial will be associated with completing the cardiorespiratory fitness test and increased physical activity in daily life. These concerns include cardiovascular and musculoskeletal events. All participants will be cleared for exercise using the PAR-Q+ [43], and if required, their family physician will be asked to assess the participants’ readiness to engage in exercise and provide a completed ePARmed-X+ [43]. Participants that are not cleared for exercise by 1 of these 2 methods will be excluded from the study. During the cardiorespiratory fitness test, participant’s blood pressure and HR will be monitored and the test will be terminated if blood pressure exceeds 220/120 mmHg or an abnormal response is recorded. The supervised exercise period is designed to gradually introduce participants to exercise by increasing the amount of physical activity performed each day. In addition, participants have the autonomy to choose their preferred exercise format (eg, walking and elliptical) for 7 of the 10 training days, further reducing the risk of musculoskeletal discomfort. Injuries sustained because of exercise will be reported. All training and supervising staff are first aid trained.

### Intervention Fidelity

To promote the fidelity of intervention delivery and to ensure the underlying BCTs are administered as intended, a comprehensive 2-day counselor training workshop will be delivered by the principal investigator (an expert in BCTs). To augment the workshop, a standard operating procedure manual will guide intervention delivery for each day of the 2-week training program and for all follow-up face-to-face contact points (ie, 3-, 6-, 9-, and 12-months). The manual consists of detailed scripts and protocols for each exercise session, phone call, or app interaction. Counselors, who will be health psychology graduate students, will complete a checklist for each training day and follow-up session to ensure all key intervention components are administered. Checklists will align with information contained within the intervention scripts, for example, *reviewed and discussed barriers sheet completed by participant.* The 2-day training workshop covers theory and BCTs targeted in the intervention and is mandatory for all counselors. Each counselor will participate in role-play activities during the workshop that will be observed by the primary investigator, and feedback will be provided. Counselors will record intervention attendance, missed sessions, session time changes, or dropout for each participant throughout the intervention and follow-up.

During the follow-up phase, counselors will be provided with standardized monthly messages to send to each participant either using the app messaging system or via email in the months when no face-to-face contact was scheduled. Counselors will record the details of all contact with participants during this time.

